### Sample size

3.6

This trial is powered to detect differences between ‘high-risk’ students (i.e. the students scoring one standard deviation above the population mean on one of the four personality types on the SURPS) in control schools vs ‘high-risk’ students in intervention schools. A total of 280 ‘high-risk’ students from 10 schools are required (i.e. 28 ‘high-risk’ students per school and 5 schools per intervention group) to achieve 80% power to detect a standardized between-group mean difference of 0.3 (p = .05) in outcomes. A between-group effect size of 0.3 is in line with effect sizes observed in previous *Preventure* trials (Newton et al., 2016). To account for dropouts, we aim to recruit 12 schools at baseline (6 per group) with 75 consenting students per school, 40% of whom are expected to screen into the program, based on previous research (Conrod et al., 2008), giving a total of 360 ‘high-risk’ students to test the effect of the intervention.

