## Methods and analysis

3

The School-led *Preventure* trial is a CONSORT-compliant cluster randomised controlled trial, to be conducted in 12 secondary schools in greater Sydney in NSW, Australia. Schools will be stratified by majority gender (i.e. >60% male or female) and randomised to either i) intervention (*Preventure*) or ii) control (health education as usual). Each condition will include 6 schools. *See*
Fig. 1.

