### Inclusion criteria

3.1

Participants must be a Year 8 student (aged approximately 13 years) in a participating school at the time of randomisation and fluent in English. Teachers may exclude students at their discretion if they believe a student will not be able to undertake the program due to learning difficulties, or if they will be disruptive to other students. Any such students will be offered alternatives, such as one-on-one delivery. This will be recorded in staff fidelity measures.

Trial sites (schools) must:i)Be a secondary or combined primary and secondary school in greater Sydney, NSW; andii)Have school principal permission to participate in the trial.iii)Have at least 60 students enrolled in Year 8 at recruitment, to ensure there are sufficient group sizes to run the intervention.

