### Statistical methods

3.10

Intention-to-treat analyses will be carried out for all primary and secondary outcomes, among the ‘high-risk’ students. Baseline equivalence and attrition between groups will be examined using single-level analyses; one-way analyses of variance (normally distributed data), chi-squared analyses (binominal data), and Mann-Whitney U-tests (non-normally distributed data). To examine intervention by time interaction effects, mixed effects regression will be used due to the multi-level nature of the data (students nested within schools). Hypothesised intervention effects on alcohol use, internalising problems and externalising problems will be examined using mixed effects linear regression analysis (continuous data) and mixed effects logistic regression analysis (categorical data). Missing data will be handled by full information maximum likelihood, in accordance with the intention-to-treat principle, which includes all randomised participants. Data from the school staff survey will be predominantly descriptive.

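### The stated inputs do not give 80% power: 280 high-risk students give about 71% for a difference of 0.3 before clustering, and less once schools are the randomised unit

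*Protocol article*

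**What the plan says.** The Sample size section (3.6) states that 280 high-risk "students from 10 schools are required", made up of 28 high-risk "students per school and 5 schools per intervention group", in order "to achieve 80% power to detect a standardized between-group mean difference of 0.3 (p = .05) in outcomes". It gives no ICC, design effect, sidedness, correlation between baseline and follow-up, or method of calculation.

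The recruitment target is larger, and the reason given is attrition: "To account for dropouts, we aim to recruit 12 schools at baseline (6 per group) with 75 consenting students per school". With 40% expected to screen in, 12 x 75 x 0.40 = 360 high-risk students, or 30 per school.

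The Methods and analysis section (3) describes a "cluster randomised controlled trial, to be conducted in 12 secondary schools". The Statistical methods section (3.10) plans mixed effects regression "due to the multi-level nature of the data (students nested within schools"), so the planned analysis recognises that students in one school are not independent.

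**The concern.** The required number, 140 per arm, is smaller than the textbook number for an individually randomised trial with the same effect size, power and two-sided 5% level. In a trial that randomises schools, correlation within schools raises the requirement. A figure below the unclustered requirement therefore cannot follow from the inputs printed beside it.

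Readers will judge the result by this sentence. If the trial finds no difference, a claim of 80% power for 0.3 SD invites the conclusion that school-led delivery does not work, when the trial may have had a much smaller chance of detecting that effect.

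**Working it through.** **Inputs from the article.** Effect d = 0.3 SD; p = .05; power 80%; k = 5 schools per arm; m = 28 high-risk students per school; so n = 5 x 28 = 140 per arm. Recruitment target: k = 6, m = 30, n = 180 per arm.

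**Assumed, because the article gives no value.** Two-sided test unless stated otherwise; ICC 0.01, 0.02 or 0.05; where baseline adjustment is considered, a baseline to follow-up correlation r of 0.5 or 0.6.

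**Step 1. The stated figure with no clustering.** Number per arm = 2 x (1.960 + 0.842)² / 0.3² = 2 x 7.849 / 0.09 = 174.4, so 175 per arm and 350 in total. With 140 per arm, the expected test statistic is 0.3 / sqrt(2/140) = 2.510. Two-sided power is Φ(2.510 − 1.960) = Φ(0.550) = 70.9%. The stated 80% is not reproduced.

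**Step 2. Adding clustering.** The design effect is 1 + (m − 1) x ICC and the expected statistic is 0.3 / sqrt(2 x design effect / n). At ICC 0.02 with m = 28, the design effect is 1 + 27 x 0.02 = 1.54, the statistic is 2.510 / sqrt(1.54) = 2.023, and power is Φ(2.023 − 1.960) = 53%. The t columns use the noncentral t distribution with (number of schools − 2) degrees of freedom.

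| ICC (assumed) | 280 in 10 schools, normal | 280 in 10, t on 8 df | 360 in 12 schools, normal | 360 in 12, t on 10 df |
|---|---|---|---|---|
| 0 | 71% | 60% | 81% | 73% |
| 0.01 | 61% | 50% | 71% | 62% |
| 0.02 | 53% | 43% | 62% | 53% |
| 0.05 | 37% | 30% | 44% | 38% |

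The 360 columns assume no loss at all, although the article adds those students to cover loss.

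**Step 3. What would bring 280 near 80%.** Each route needs something that the Sample size section does not state. The variance factor multiplies the variance of the difference.

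- One-sided 5% test, no clustering: Φ(2.510 − 1.645) = 80.7%.
- Change score with r = 0.6, two-sided, no clustering: variance factor 2(1 − 0.6) = 0.8; number per arm 0.8 x 174.4 = 139.5; power 80.1% at 140.
- Baseline-adjusted single follow-up, r = 0.6, ICC 0.01: variance factor 1 − 0.6² = 0.64, design effect 1.27; power 79.5% by normal approximation, 68.5% with t on 8 df.
- Baseline-adjusted mean of both follow-ups, all correlations 0.5, ICC 0.02: variance factor (1 + 0.5)/2 − 0.5² = 0.50, design effect 1.54; power 82% by normal approximation, 71% with t on 8 df.

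The first two routes contain no clustering allowance and the last two do. All land near 80% by normal approximation, so the number 280 does not reveal which was used.

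**The case against.** The strongest reply is that this is a condensed article. The full protocol may hold an ICC, a correlation and a proper multilevel calculation, and leaving those to it is not an error. The requirement is laid out as students per school and schools per arm, which suits a multilevel calculation. The trial also has a baseline and two follow-ups analysed by mixed models, so some gain in precision over a single cross-sectional comparison is likely. With all correlations at 0.6, averaging both follow-ups with baseline adjustment at ICC 0.01 gives 84% for 280 students even with t on 8 df. A stable school effect would also partly cancel on adjustment for baseline, so applying the full design effect may be pessimistic.

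Much of this stands. It rules out asserting that clustering was ignored. A reader might infer that from 280 falling below the unclustered requirement, but the last two routes in Step 3 allow for clustering and still come near 80%, so the article does not settle it.

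It does not rescue the sentence as written. The complaint is not that an ICC is missing. The article prints an effect size, a level, a sample size and a power; describes the effect as a plain between-group mean difference; and those figures do not agree under the usual two-sided reading.

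**Conclusion.** The point holds in this form: as described, 280 high-risk students in 10 schools do not give 80% power for a mean difference of 0.3 at a two-sided 5% level. They give 70.9% with no clustering. For a cluster design without variance reduction, power is about 61% to 37% over ICCs of 0.01 to 0.05 by normal approximation, or 50% to 30% with t on 8 df. The 70.9% rests only on the printed inputs and a two-sided test; the clustered figures also rest on assumed ICCs.

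Three further inferences are not supported. That true power is close to one half holds under some assumptions only. That a school at the 60-student enrolment minimum (Inclusion criteria, 3.1) cannot supply 28 high-risk students treats the expected 40% as a ceiling and an eligibility minimum as the planned average. That the claim fails for the binary alcohol outcomes goes beyond the text, which claims power for a standardised mean difference only.

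**What to change.** Replace the power sentence with one that states whether the test is one- or two-sided, the ICC, the baseline to follow-up correlation, the analysis assumed (single follow-up, change score, baseline-adjusted, or both follow-ups combined) and the degrees of freedom. The values should be the sponsor's own, with their source. Give the resulting power, or the detectable difference at 80% power, both for 280 students in 10 schools and for 360 in 12.

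If those inputs yield 80%, the sentence then supports itself. If they do not, restate the figure. As an illustration only, with assumed ICC 0.02, r = 0.6, baseline adjustment, one follow-up and a two-sided t test on 8 or 10 df, power is about 60% for 10 x 28 and 72% for 12 x 30.

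This changes wording only. It needs no extra schools or students and no change to the analysis; the cost is that the stated power may be less favourable.

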### Recruitment and consent

3.7

All eligible schools in greater Sydney will be approached using publicly available contact details. The study will also be promoted to schools through professional networks. School Principals will be sent an invitation letter via email describing the study and seeking permission to implement the study in their school. Schools will be followed up with phone calls to discuss enrolment. Principals who agree for their school to participate, and who are randomised to the intervention group, will identify two to four staff members who may be interested in participating in the trial. Staff members will receive further information about the trial, and if they decide to participate, they will be asked to complete consent forms, agreeing to undertake the *Preventure* training, coordinate information and consent procedures, deliver the *Preventure* groups, and complete an evaluation survey of the *Preventure* program and its implementation.

Once the schools have been randomised, they will be sent the information and consent forms for parents/guardians of Year 8 students in the school, and will be asked to send these to the parents/guardians via their usual communication method. Students who receive active parental consent (opt in) must also provide their own consent before beginning the study. Participants are informed that they are free to withdraw from the study at any time.

### Allocation

3.8

Blocked randomisation of schools to *Preventure* and control, stratified by school gender mix [co-educational, predominately male (>60%), or predominately female (>60%)], will be performed by an external researcher using the Blockrand package in R (Snow, 2020). Allocation concealment is ensured as the external researcher does not release the randomisation until the school has been irreversibly allocated to a condition. Schools will not be masked to their allocation and will be informed whether they are in the intervention or control group. Participants (i.e. students) will be blinded to the hypotheses of the study. As is the case for school-based interventions of this kind, students, teachers, and researchers will be aware of the schools’ allocation.

### Data collection methods and data management

3.9

All students (intervention and control conditions) will be asked to complete an online self-report survey in class at baseline (prior to the intervention), and 6- and 12-months post-baseline. Students will enter a unique identifier and will enter this code each time they complete a questionnaire. The student’s data files will be linked over time with this unique code, whilst maintaining confidentiality. Responses to the SURPS (Woicik et al., 2009) will be linked to this unique code; scores on the SURPS will be used to classify students into groups, and once classified the codes will be re-identified in a separate database and sent to the school contact in a secure link. Contact details will be marked as identifiers and access restricted. Students will be made aware that all contact information will be kept confidential and secure, separate from their survey responses.

School staff in the intervention condition will complete an online survey to collect the implementation outcomes (e.g., feasibility, acceptability) of *Preventure.* The survey contains a mix of closed and open-ended questions. Intervention students and staff will also complete a brief paper-based evaluation survey at the end of the last workshop. A paper-based survey was chosen for ease of completion immediately post-group. For students, the evaluation survey includes both open and closed questions, such as what they liked/disliked about *Preventure* and whether the information covered was helpful. For staff, the evaluation survey will measure implementation fidelity, that is, their adherence to the intervention. No identifying information will be collected in these surveys. All data collected on paper surveys will be entered into an electronic database on the University of Sydney server.

To maximise retention, students who are absent on the days of data collection will be contacted by school staff to offer an alternate time to complete the survey. Additionally, student participants will be entered into a prize draw to win a $50 gift voucher for each survey they complete. Staff in both intervention and control schools will receive a reimbursement of $50 for their time at the conclusion of the study.

### Statistical methods

3.10

Intention-to-treat analyses will be carried out for all primary and secondary outcomes, among the ‘high-risk’ students. Baseline equivalence and attrition between groups will be examined using single-level analyses; one-way analyses of variance (normally distributed data), chi-squared analyses (binominal data), and Mann-Whitney U-tests (non-normally distributed data). To examine intervention by time interaction effects, mixed effects regression will be used due to the multi-level nature of the data (students nested within schools). Hypothesised intervention effects on alcohol use, internalising problems and externalising problems will be examined using mixed effects linear regression analysis (continuous data) and mixed effects logistic regression analysis (categorical data). Missing data will be handled by full information maximum likelihood, in accordance with the intention-to-treat principle, which includes all randomised participants. Data from the school staff survey will be predominantly descriptive.

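### The student-level tests planned for baseline equivalence and attrition ignore school clustering, so their false-positive rate exceeds 5% at any positive intraclass correlation

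*Protocol article*

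**What the plan says.** All references are to the protocol article.

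- **Baseline and attrition checks (3.10 Statistical methods).** "Baseline equivalence and attrition between groups will be examined using single-level analyses". The tests named are one-way ANOVA for normal data, chi-squared for binary data and Mann-Whitney for non-normal data. None has a term for school.
- **Outcome models (3.10).** For intervention-by-time effects the next sentence changes approach and gives the reason: the models are mixed "due to the multi-level nature of the data (students nested within schools").
- **Unit of allocation (3.8 Allocation).** "Blocked randomisation of schools", stratified by school gender mix.
- **Numbers (3.6 Sample size).** "we aim to recruit 12 schools at baseline (6 per group) with 75 consenting students per school", of whom 40% are expected to screen in, "giving a total of 360 ‘high-risk’ students to test the effect of the intervention".
- **Order of events (3.7 Recruitment and consent).** Consent forms reach parents only after the school has been randomised. Section 3.8 adds that allocation is not masked.
- **Data collection (3.9).** Students "complete an online self-report survey in class". Absent students are to be offered another time.

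Nothing in the article adds a cluster correction to the baseline and attrition tests or says that they are only descriptive.

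**The concern.** The three named tests treat each student as an independent observation of the arm effect. Arm is assigned to schools, so the comparison rests on 6 schools against 6, not on 180 students against 180. If students in a school resemble one another at all on the variable tested, the single-level standard error is too small and so is the p-value. The article recognises this structure for the outcomes and drops it when it compares the same students between the same arms.

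This is a stated method, not detail left to an analysis plan. It matters because students enter after allocation and under open allocation. Selective consent and differential loss are therefore real possibilities, and these are the checks the article names that bear on them. A test that cannot separate an arm difference from ordinary school-to-school variation does not answer that question.

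**Working it through.** **Inputs from section 3.6.** 12 schools, 6 per arm; 75 consenting students per school; 40% screening in.

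- High-risk students per school: 75 × 0.40 = 30.
- Per arm: 6 × 30 = 180. Total: 360, which reproduces the article's own figure.

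**Assumed input.** The article gives no ICC. The range 0.01 to 0.10 is used for illustration.

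**Formula.** Design effect DE = 1 + (m − 1) × ICC with m = 30, so DE = 1 + 29 × ICC. A single-level test understates the standard error by a factor √DE, so its true two-sided type I error is 2 × [1 − Φ(1.96/√DE)].

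| ICC (assumed) | DE | 1.96/√DE | True type I error | Effective students per arm (180/DE) |
|---|---|---|---|---|
| 0 | 1.00 | 1.96 | 5% | 180 |
| 0.01 | 1.29 | 1.73 | 8.4% | 140 |
| 0.02 | 1.58 | 1.56 | 11.9% | 114 |
| 0.05 | 2.45 | 1.25 | 21% | 73 |
| 0.10 | 3.90 | 0.99 | 32% | 46 |

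**Check by simulation.** Null trials with 6 schools per arm and 30 students per school were simulated: 20,000 per setting for ANOVA and chi-squared, 2,000 for Mann-Whitney. The chi-squared runs assume 20% dropout.

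| ICC | ANOVA | Chi-squared (attrition) | Mann-Whitney | t-test on school means |
|---|---|---|---|---|
| 0 | 5.1% | 5.0% | 4.8% | 5.1% |
| 0.01 | 8.5% | 8.4% | 7.6% | 5.0% |
| 0.02 | 12.0% | 11.8% | 11.2% | 4.9% |
| 0.05 | 21.5% | 21.3% | 20.5% | 5.3% |
| 0.10 | 33.3% | 32.8% | 32.6% | 5.1% |

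All three planned tests follow the formula. The school-level comparison holds its level.

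**Loss of one whole school.** Suppose one intervention school withdraws and nobody else is lost.

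- Planned test: 30/180 against 0/180. Pooled proportion 30/360 = 0.0833; standard error √(0.0833 × 0.9167 × 2/180) = 0.0291; z = 0.1667/0.0291 = 5.72; chi-squared = 32.7; p about 1 × 10⁻⁸.
- School level: proportions lost are 1, 0, 0, 0, 0, 0 against six zeros. Difference in means 1/6; variance in the affected arm 1/6; standard error √((1/6)/6) = 1/6; t = 1.0 on 10 df; p = 0.34.

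**Cost of the valid attrition test.** With 20% dropout (assumed), the standard error of the arm difference is √(2 × 0.2 × 0.8/180 × DE). Power is taken from the noncentral t on 10 df.

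| ICC | SE of difference | Power for a true 10-point difference | Difference needed for 80% power |
|---|---|---|---|
| 0.01 | 4.8 points | 47% | 15 points |
| 0.05 | 6.6 points | 28% | 21 points |
| 0.10 | 8.3 points | 19% | 26 points |

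**The case against.** **No efficacy conclusion uses these p-values.** This stands. Section 3.10 assigns every hypothesised effect to mixed models, with missing data handled by full information maximum likelihood. A reader might infer that the treatment-effect estimates are compromised, or that adjustment covariates will be picked from the baseline tests. The article supports neither: it does not link these tests to the outcome models or to covariate choice.

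**The size is unknown.** This also stands. At an ICC of 0 there is no inflation, and at 0.01 it is modest. Stratification by gender mix would reduce it for variables related to gender mix. It would be too strong to say that the tests are bound to report false differences.

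**Clustering of attrition is inferred.** In-class surveys suggest that a missed session could remove a block of students, but section 3.9 provides catch-up times, which weakens that route. It does not cover withdrawal of a whole school. Section 3.6 goes from 10 schools to 12 to allow for dropouts, so loss of schools is not remote.

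**The error is in the cautious direction, and the valid test is weak.** Ignoring clustering over-flags imbalance and does not hide it, while a 10 df test may miss a real 10-point difference in loss. The low power is real and must be disclosed. It does not justify the planned tests, whose apparent sensitivity comes from an understated standard error. The answer is to report an interval rather than rely on either p-value.

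**Conclusion.** The point holds as a limited flaw in supporting analyses. The planned single-level tests are inconsistent with randomisation by school and with the article's own reason for using mixed models. Their type I error exceeds 5% at any positive ICC: about 8%, 12%, 21% and 32% at 0.01, 0.02, 0.05 and 0.10. These figures assume 30 high-risk students in each of 6 schools per arm and ICCs that the article does not state.

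The consequence is that evidence of baseline imbalance or differential attrition would be overstated, most visibly if a whole school is lost. The primary effect estimates are untouched. The point deserves correction because recruitment after randomisation makes these checks informative about bias.

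**What to change.** Replace the single-level tests in section 3.10.

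- **Baseline.** Describe characteristics by arm with standardised differences. If a test is wanted, use a model that includes school.
- **Attrition.** Compare arms by school-level proportions (t on 10 df with 12 schools) or by a mixed logistic model with a random effect for school.
- **Reporting.** Give the attrition difference with its confidence interval and list attrition by school. State that power is low with 12 schools and that a non-significant result is not evidence of no differential loss.

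The cost is a change of wording and a little code. Design, data collection and sample size do not change. The drawback is a less sensitive attrition test, which the interval and the school-level listing make visible.

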### Outcomes

3.5

The primary outcomes are differences in the prevalence and/or means of ‘high-risk’ students in the intervention and control schools on alcohol use, internalising problems (anxiety and depressive symptoms) and externalising problems (conduct problems and hyperactivity symptoms), at 6- and 12-months post baseline. Specifically, it is hypothesised that ‘high-risk’ students in the intervention group will have lower prevalence/scores than ‘high-risk’ students in the control group, on the following primary outcome measures:i)Alcohol use

A series of questionnaires adapted from the School Health and Alcohol Harm Reduction Project ‘Patterns of Alcohol’ index (McBride et al., 2004) will be used to measure intention to try alcohol, any use of alcohol ever (at least a standard drink), the frequency and quantity of alcohol consumption in standard drinks in the past six months, and frequency of binge drinking (five or more standard drinks on one occasion) in the past six months. Alcohol-related harms will be measured with an abridged form of the Rutgers Alcohol Problem Index (RAPI) (White and Labouvie, 1989). The original scale shows high internal consistency with adolescent samples (White and Labouvie, 1989). These questions were used in the previous Australian trial of *Preventure* (Newton et al., 2016, Newton et al., 2012).ii)Internalising problems

The ‘Kessler 6′ scale (K6) (Kessler et al., 2002) will be used to assess psychological distress in the past month. The K6 shows high accuracy, consistency across samples, and specificity (Kessler et al., 2002). Depressive symptoms will be measured using the ‘Patient Health Questionnaire, modified for adolescents (PHQ-A) (Johnson et al., 2002), which demonstrates good sensitivity and specificity, diagnostic validity and accuracy (Johnson et al., 2002). Anxiety symptoms will be measured by the ‘Generalised Anxiety Disorder 7-item scale’ (GAD-7), which shows strong reliability and validity (Spitzer et al., 2006).iii)Externalising problems

The conduct problems and hyperactivity subscales of the Strengths and Difficulties Questionnaire (SDQ) (Goodman, 1997) will be used to assess externalising problems. These subscales have been confirmed with a five-factor structure demonstrating satisfactory reliability and validity, predicting an increased likelihood of psychopathology (Goodman, 2001).

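### The analysis is framed as an intervention-by-time interaction, while the outcome and power sections concern the between-arm difference at 6 and 12 months; a baseline-adjusted difference estimates that more precisely from data already collected

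*Protocol article*

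**What the plan says.** All references are to the protocol article.

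- **Outcomes (3.5):** "The primary outcomes are differences in the prevalence and/or means of ‘high-risk’ students in the intervention and control schools", assessed "at 6- and 12-months post baseline". Both visits are primary.
- **Sample size (3.6):** the target is a "standardized between-group mean difference of 0.3", with 80% power at the .05 level. The stated requirement is: "A total of 280 ‘high-risk’ students from 10 schools are required". This is made up of five schools in each arm, each contributing 28 such students. The recruitment aim is 12 schools of 75 students with 40% screening in, so 30 per school and 360 in all. No ICC, sidedness or baseline to follow-up correlation is given.
- **Statistical methods (3.10):** "To examine intervention by time interaction effects, mixed effects regression will be used", with students nested in schools, linear models for continuous data, logistic models for categorical data, and full information maximum likelihood for missing data. Baseline is mentioned only for single-level checks of equivalence. No model covariates are listed and the coding of time is not given.
- **Allocation (3.8):** randomisation of schools is "stratified by school gender mix", in three levels.
- **Data collection (3.9):** every student is asked to complete the survey at baseline, 6 and 12 months, linked by code, so baseline values of the outcomes are planned data.

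**The concern.** The article defines and powers one contrast, the difference between arms at follow-up, and names another, the interaction of arm with time. In the usual reading, with baseline as one of the repeated outcomes and a free baseline mean in each arm, the interaction at a visit is the difference between arms in change from baseline. That contrast carries the full noise of the baseline measurement. When r is below 0.5 it is even less precise than ignoring baseline altogether.

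Two things are at stake. The first is power, which is scarce when 12 schools are the randomised units. The second is clarity about the reported estimate. A linear-time slope difference, or a joint test over visits, is not the difference at 6 months or at 12 months that the Outcomes section defines.

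**Working it through.** **1. The plan's own figure.** For a plain follow-up difference of d = 0.3 with no clustering, n per arm = 2(z_α + z_β)²/d².
- One-sided 5%: 2(1.645 + 0.842)²/0.09 = 137.4, so 138 per arm and 276 in total. Power at 140 per arm is 80.65%.
- Two-sided 5%: 2(1.960 + 0.842)²/0.09 = 174.4, so 175 per arm and 350 in total. Power at 140 per arm is 70.9%.

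So 280 is reproduced as a follow-up difference only if the test is one-sided and the ICC is zero. It also fits a two-sided interaction test at ICC 0 with r about 0.6 (80.1%). The section states no such correlation and describes a mean difference.

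**2. Variance of the two contrasts** (continuous outcome, relative to a follow-up-only comparison).
- Difference in change: 2(1−r).
- Baseline-adjusted difference: 1−r².
- Ratio of adjusted to change: (1−r²)/[2(1−r)] = (1+r)/2. This is 0.75 at r = 0.5 and 0.80 at r = 0.6, and below 1 for every r < 1.

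**3. Power at the recruitment target.**
- From the article: 12 schools, 30 high-risk students each (180 per arm), d = 0.3.
- Assumed: ICC 0.02, two-sided 5%, no dropout, the same r applied to school means.
- Design effect = 1 + 29 × 0.02 = 1.58.
- Follow-up-only variance = 2 × 1.58/180 = 0.01756, SE 0.1325.

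Power is from the noncentral t. The change contrast gets 12 − 2 = 10 df (critical t 2.23). The adjusted model gets 8 df (critical t 2.31), because three-level school gender mix takes 2.

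| r | Change: SE, d/SE, power | Adjusted: SE, d/SE, power |
|---|---|---|
| 0.3 | 0.157, 1.91, 41% | 0.126, 2.37, 55% |
| 0.5 | 0.132, 2.26, 53% | 0.115, 2.61, 63% |
| 0.6 | 0.119, 2.53, 63% | 0.106, 2.83, 70% |
| 0.7 | 0.103, 2.92, 75% | 0.095, 3.17, 79% |

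Without charging the 2 df, the adjusted figures at r = 0.5 and 0.6 would be 66% and 72%. The proposed model includes the stratum, so 63% and 70% are the fair ones.

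**4. Sensitivity to stable school differences.** Suppose school effects correlate 0.8 over time and the within-student correlation is 0.5 (both assumed). The correlation of school means is then (30 × 0.02 × 0.8 + 0.98 × 0.5)/1.58 = 0.614.
- 12 × 30: 64.2% for change against 71.0% adjusted, with 8 df for the latter.
- 10 × 28, where r = 0.609: 52.0% against 57.0%, with 8 and 6 df.

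The gain is 5 to 7 points.

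**5. What the interaction estimates.**
- Categorical visit, free baseline means: expectation (follow-up difference) − (baseline difference). Randomisation makes the second term zero on average, so the target is the same and only precision differs.
- Linear time: a slope difference.
- Joint test: no single difference is estimated.

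The article does not say which applies.

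**The case against.** The strongest reply is that one summary sentence is being read too closely. An arm-by-visit term is itself an intervention-by-time interaction, and the recommended model contains one. The sentence also fits a model with a common baseline mean, whose interaction terms are essentially baseline-adjusted differences. Coding of time and choice of covariates are usually left to an analysis plan that is not shown. This stands in part: the absence of a covariate list is not a fault, and the loss of precision depends on baseline means being free by arm. What remains is that the article names a contrast other than the one it defines and powers, and does not tie the two together.

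Three stronger readings are tempting, and the document does not support them.

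- **That the planned estimate is the wrong quantity.** With categorical time it has the right expectation under randomisation. The Objectives also speak of preventing onset or escalation, for which change over time is a natural framing.
- **That leaving out school gender mix distorts the test.** That could happen in a follow-up-only comparison with no baseline adjustment, but this is neither the named analysis nor the recommended one. Stable differences between strata cancel in a change contrast. A simulation with an assumed ±0.25 SD between strata (four schools in each, r = 0.5) gave 5.1% type I error and 53% power without the stratum term, and about 5% and 51% with it.
- **That the change is pure wording and suits every outcome.** Lifetime alcohol use cannot revert if reported consistently, so a logistic model with its own baseline value as covariate separates. Using only follow-up values as outcomes would also drop students with baseline data alone, against the stated likelihood approach.

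**Conclusion.** The point holds as one of precision and of a clearly stated estimate. For continuous outcomes, an interaction with free baseline means is less precise than a baseline-adjusted difference at any r below 1. At 12 × 30 with ICC 0.02, the cost is about 10 points of power at r = 0.5 and 7 points at r = 0.6. It is about 5 to 7 points if school effects are strongly stable and the within-student correlation is 0.5. If time is linear or the test joint, the result also fails to report the difference that the Outcomes section defines.

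The ICC, the correlations, the two-sided test and complete follow-up are assumptions. The direction of the variance comparison does not depend on them, but the size does. The formulas do not carry over directly to the logistic models. The change is worth making, though the plan would not be invalid without it.

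**What to change.** - **Continuous outcomes.** State the primary estimate as the between-arm difference at 6 months and at 12 months, from a mixed model with arm, visit, arm-by-visit, the baseline value of that outcome and school gender mix. Keep both visits primary, as the Outcomes section has them.
- **Missing data.** Handle baseline within the likelihood so that students with baseline data only remain in the analysis, as the Statistical methods section intends. Parental consent is sought after schools are randomised (Recruitment and consent), so baseline imbalance is possible. That is a further reason to condition on baseline.
- **Binary outcomes.** Use the logistic counterpart and adjust for baseline where it can be estimated. For lifetime alcohol use, analyse uptake among students who had not used at baseline. Uptake is already among the hypotheses in the Objectives.

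**Cost.** No new data are needed. The stratum terms take 2 of 10 school-level degrees of freedom (critical t from 2.23 to 2.31), or 2 of 8 if only 10 schools remain, and may add little once baseline is in the model. The uptake analysis gives up baseline users for that one outcome.
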